### Sample size {14}

The sample size was calculated for the primary outcome of the child-reported overall pain score. We consider a 30% reduction in the pain NRS score as a minimal clinically meaningful reduction in pain. According to our previous publication on pain reduction of VR-PAT among pediatric patients 6–17 years of age who were treated at our outpatient burn clinic [19], the pooled standard deviation (SD) of the child-reported overall pain visual analog scale (VAS) score was estimated. Aiming at detecting a 30% reduction of the pain score in the VR-PAT group compared with the control group at any of the first 7 days of follow-up, and assuming the same SD on these days, we will need 89 subjects per group to achieve 80% power and a two-sided type-I error of 0.01 at each day using a two-sample *t*-test. The type-I error rate is adjusted by Bonferroni correction for multiple comparisons. Assuming a 10% dropout rate, we will need 99 subjects per group. Based on this calculation, we plan to *n* = 100 subjects per group (*n* = 200 subjects total).

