## Statistical methods

### Statistical methods for primary and secondary outcomes {20a}

#### Aim 1

In the primary analysis, the child-reported overall pain NRS score will be compared between the VR-PAT and control groups during each of the first 7 days of follow-up using a two-sample *t*-test. The *p* values will be adjusted by Bonferroni correction to account for multiple comparisons and then compared to the critical value of 0.05 to determine statistical significance. In the secondary analysis, child-reported worst pain score, parent-observed overall and worst pain scores, child engagement and experience with VR, caregiver report of VR use, and adverse effects related to engagement with VR will be compared between the two study groups using a two-sample *t*-test (for continuous variables) and chi-squared test (for categorical variables). To estimate the overall difference in the child-reported overall pain score between the two study groups over the 7 days of follow-up, a linear mixed effect model with random intercept accounting for the correlation among repeated measures of pain scores will be fit. The dependent variable of the model will be child-reported overall pain score. The independent variables of the model will contain the study group, time (follow-up days), and any potential confounders deemed unbalanced between the study groups. The coefficient of the study group is the estimated overall difference in the pain score. To further explore whether the trend of child-reported overall pain score over the 7 days differs between study groups, the same linear mixed effect model as above will be fit with the addition of interaction between the study group and time. The coefficient of the interaction term estimates the difference in the trend of pain scores over time.

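### Single-step Bonferroni on the seven daily primary tests is valid but gives away power that Holm's step-down procedure would keep at the same family-wise error rate

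*Protocol article*

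**What the plan says.** In the protocol article, Statistical methods for primary and secondary outcomes {20a}, Aim 1, the primary analysis is a family of seven two-sample t-tests: "the child-reported overall pain NRS score will be compared between the VR-PAT and control groups during each of the first 7 days of follow-up". The p "values will be adjusted by Bonferroni correction to account for multiple comparisons" and are "then compared to the critical value of 0.05 to determine statistical significance". Each day therefore gets its own verdict of significant or not.

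Sample size {14} uses the same correction: "The type-I error rate is adjusted by Bonferroni correction for multiple comparisons". It plans on "a two-sided type-I error of 0.01 at each day" and concludes that "we will need 89 subjects per group to achieve 80% power". Neither section mentions a step-down procedure or gives a reason for preferring the single-step one.

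**The concern.** Single-step Bonferroni holds all seven days to 0.05/7, however many of the other days have already been shown to differ. Holm's procedure relaxes the threshold after each rejection and still keeps family-wise error at 0.05 with no assumption about dependence. Dependence matters here because the seven scores come from the same child and their correlation is unknown.

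The first rejection needs the same p value under both methods, so the difference lies in the second and later days. Those days count because the primary analysis reports a result for each day. If the benefit lasts through the week, some days with a real effect would be labelled non-significant that Holm would have declared significant, with the same children and the same error rate.

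**Working it through.** **Inputs from the protocol.** Seven daily tests and family-wise alpha 0.05 (section {20a}); 89 per group, 80% power and two-sided 0.01 per day (section {14}); 1:1 allocation (Trial design {8}).

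**Assumptions.** Neither the control mean nor the SD is given, so the 30% reduction cannot be turned into a standardized difference and the 89 cannot be rebuilt from stated inputs. I solved backwards: a two-sample t-test with 89 per group, 80% power and two-sided alpha 0.01 implies d = 0.517 (normal approximation: 0.512). The between-day correlation is not given either; I used equal correlations of 0.3 to 0.7, with 0 and 0.8 as wider checks.

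**Plan's own figures.** Dropout: 89/0.90 = 98.9, so 99 per group, which agrees. Per-day alpha: 0.05/7 = 0.00714, whereas the stated 0.01 is 0.05/5, which does not agree.

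**The two rules.** Order the p values p(1) ≤ ... ≤ p(7).
- Bonferroni rejects every day with p ≤ 0.05/7 = 0.00714.
- Holm compares p(1) with 0.05/7 = 0.00714, p(2) with 0.05/6 = 0.00833, then 0.05/5 = 0.01, 0.05/4 = 0.0125, 0.05/3 = 0.0167, 0.05/2 = 0.025 and 0.05/1 = 0.05, and stops at the first failure.

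Holm's thresholds are never below Bonferroni's, so it rejects at least the same days. Its error control follows from Bonferroni itself. If m of the days are true nulls, the first true null that Holm rejects must have p ≤ 0.05/m, and the chance that any of m true nulls does so is at most m × 0.05/m = 0.05, whatever the correlation.

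**Simulation.** Seven correlated two-sample t-tests, 89 per group, d = 0.517 on affected days. Average power per affected day, correlations 0.3 to 0.7:

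| True effect | Bonferroni | Holm |
|---|---|---|
| All 7 days | 76-77% | 85-88% |
| Fading linearly to 40% (d = 0.207) by day 7 | 40-41% | 47-48% |
| 5 of 7 days | 76-77% | 81-82% |
| 3 of 7 days | about 77% | about 79% |
| 1 of 7 days | about 76.5% | about 76.5% |

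With the effect on all seven days, the mean number of days found rises from about 5.3-5.4 to 6.0-6.1, and the chance of finding all seven from 30-49% to 65-75%. At correlations of 0 and 0.8 the per-day figures under Holm are 89% and 84%, against about 76.5% for Bonferroni.

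**Checks.** In no run did Bonferroni reject a day that Holm missed. The two methods never differed on whether at least one day was significant. Holm's family-wise error was at most 0.048 in every scenario with true nulls. When no day has an effect the two methods have the same family-wise error: 0.048, 0.040 and 0.027 at correlations 0, 0.5 and 0.8.

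**The case against.** The strongest reply is that nothing here is wrong: Bonferroni is prespecified, simple and controls the family-wise error strongly. That stands. A reader might infer that the present plan fails to control type I error, and the protocol does not support that reading. The point concerns efficiency only.

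Second, section {14} can be read as aiming at a reduction on at least one of the seven days. On that reading Holm gains nothing, because its first step is Bonferroni's. This also stands, but the same section states its error level per day and section {20a} tests every day, so the per-day reading is at least as natural.

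Third, the gain depends on how many days are affected. It is largest when the benefit persists and vanishes when only one day is affected. This stands, and the table shows it.

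Fourth, a reader might infer that Bonferroni would distort the picture of when VR works during the week. That goes too far. Section {20a} also plans a mixed model for the overall seven-day difference and a group-by-time interaction for the trend, and these describe the time course better than seven significance labels do. In the fading scenario Holm itself still misses about half of the daily effects; detection on day 7 rises only from about 10% to 17-21%.

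Fifth, the fact that Bonferroni's error falls below 5% under the global null might be offered as slack for Holm to use. It is not: Holm's error there is identical, and the slack comes from the between-day correlation, which Holm does not exploit.

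**Conclusion.** The point holds as an optional improvement of low severity. Holm dominates single-step Bonferroni for these seven tests: same error guarantee, no added assumption, no day lost. The gain is about 8 to 12 points of per-day power with the design effect on all seven days, about 7 points with a fading effect and about 2 points with three affected days. It is nil with one affected day or for at least one significant day. The ordering of the methods is a mathematical fact. The sizes rest on the back-solved d = 0.517 and the assumed correlations.

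It should not be inferred that the sample size could be reduced, or that the 0.01 per-day level can stay as a cautious planning value. That level is looser than 0.05/7, which is also Holm's first threshold. At 0.05/7, 89 per group gives about 76.6% power, and about 96 per group (96/0.90 = 106.7, so 107 with 10% dropout) would be needed for 80%. That mismatch must be dealt with separately.

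**What to change.** In section {20a}, Aim 1, replace *Bonferroni correction* by *Holm step-down adjustment* for the seven daily p values, and compare the adjusted values with 0.05 as now. The tests, the endpoint and the number of children stay the same.

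The wording change is short, but it alters the analysis plan of a trial that has been recruiting since January 2023. It therefore needs the amendment route in Plans for communicating important protocol amendments {25}: IRB submission before implementation and a registry update as appropriate. No interim analysis is planned and completion is expected by April 2027, so it can be made before primary results are seen; the amendment should say so.

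The statistical cost is that simultaneous confidence intervals matching Holm are less simple. Bonferroni intervals for the daily differences can still be reported alongside, with a note that an interval may include zero on a day that Holm declares significant.

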#### Child surveys (self-reported)

All participants (control and intervention group) will self-report anxiety prior to the dressing change using the STAI-CH scale with ratings from not at all to very much. After the dressing change is completed, the child will answer the remaining survey questions assessing overall pain score (NRS, 0–10), worst pain score (NRS, 0–10), and time spent thinking about pain (NRS, 0–10). The survey is completed once daily alongside dressing changes for 7 days until the patient returns for their follow-up appointment. Survey questions remain the same for each daily dressing change.

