#### Guardian surveys (proxy report)

Caregivers (control and intervention group) of the participating child conducting the dressing change are asked to report their observation of the child’s pain after wound care (NRS, 0–10). Caregivers are also asked to document any opioid or pain medication given (name, brand, and dose) and are given the opportunity to share anything of note for that dressing change. The survey remains the same for each day of wound care and is to be completed once daily after the child surveys.

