### Methods for additional analyses (e.g., subgroup analyses) {20b}

Survey questions not listed as primary or secondary outcomes will be compared between the two study groups at each of the 7 days of follow-up. Subgroup analyses will be conducted by performing the same analyses as described above separately by sex and age (6–9 vs. 10–14, 15–17 years of age).

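### Worst pain and caregiver-observed pain, scored daily for about a week, are compared by t-tests with no stated unit of analysis or multiplicity rule, while the planned mixed model is kept for child-reported overall pain only

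*Protocol article*

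**What the plan says.** Both pain surveys are repeated daily. For the child, "The survey is completed once daily alongside dressing changes for 7 days until the patient returns for their follow-up appointment" (Child surveys). For the caregiver, "The survey remains the same for each day of wound care and is to be completed once daily after the child surveys" (Guardian surveys).

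The primary Aim 1 analysis in {20a} compares child-reported overall pain on each of 7 days. For those tests the p "values will be adjusted by Bonferroni correction to account for multiple comparisons and then compared to the critical value of 0.05".

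The secondary analysis comes next: "In the secondary analysis, child-reported worst pain score, parent-observed overall and worst pain scores, child engagement and experience with VR", together with caregiver-reported VR use and adverse effects, "will be compared between the two study groups using a two-sample" t-test, or by chi-squared test if categorical. No day, average or other unit is named, and no adjustment is attached.

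The section then plans "a linear mixed effect model with random intercept accounting for the correlation among repeated measures of pain scores will be fit". Its scope is explicit: "The dependent variable of the model will be child-reported overall pain score".

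Section {20b} adds further daily testing: "Survey questions not listed as primary or secondary outcomes will be compared between the two study groups at each of the 7 days" of follow-up. Again no adjustment is stated.

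Outcomes {12} places child- and caregiver-reported worst and average pain, and time spent thinking about pain, under the primary outcome measure. Section {20a} treats worst pain and the caregiver ratings as secondary, and its Aim 1 text does not name time spent thinking about pain.

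**The concern.** A t-test takes one value per child, and these ratings produce up to seven. The secondary sentence does not say how seven become one. The natural reading follows the sentence before it, which tests day by day. That would give a table of daily p values for each rating with no rule on how many may be read as findings.

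A claim about worst pain or caregiver-seen pain could then rest on whichever days fall below 0.05. The trial's question, as the Abstract puts it, concerns the difference over the week of dressing changes. Daily tests do not give one answer to it. The plan already has the suitable tool, and for Aim 2 it extends the same model to the secondary fun and realism scores. The Aim 1 secondary pain ratings get no such extension.

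**Working it through.** **The plan's own figures.** The document states no error rate for the secondary tests. Its sample-size figures concern the primary outcome: 89 per group, and 89 / (1 − 0.10) = 98.9, so 99, which agrees. The 89 cannot be rebuilt because the mean and SD are not printed. At 80% power and two-sided 0.01 it implies a standardised difference of about 0.52.

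**Inputs from the document.** Three secondary pain ratings (child worst, caregiver overall, caregiver worst) and 7 daily surveys. Threshold 0.05, taken from the primary rule because none is given for these ratings.

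**Assumed inputs.** The documents give no correlations. I take 0.4 to 0.8 between ratings on the same day and 0.4 to 0.8 between days for the same rating. The correlation between different ratings on different days is the product of the two.

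**Step 1: number of tests, per-day reading.** 3 × 7 = 21.

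**Step 2: chance of at least one p < 0.05 with no effect.** If all 21 were independent: 1 − 0.95^21 = 65.9%. That is an outer bound, because the ratings are correlated. Simulating 21 correlated z statistics with |z| > 1.96:

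| Between ratings | Between days | At least one p < 0.05 |
|---|---|---|
| 0.4 | 0.4 | 55% |
| 0.5 | 0.5 | 49% |
| 0.8 | 0.6 | 36% |
| 0.8 | 0.8 | 27% |

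**Step 3: fewer days.** Eligibility {10} requires daily changes for about 5 days. With 5 days there are 3 × 5 = 15 tests, and the figure is 30 to 45% for between-day correlation 0.4 to 0.6. At 0.8 for both correlations it is about 23%.

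**Step 4: one week-level test per rating.** Three tests: 1 − 0.95^3 = 14.3% if independent, and 13% to 10% with between-rating correlation 0.4 to 0.8. With Bonferroni or Holm across the three it is at most 5%.

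**Step 5: precision.** Assume a constant difference d = 0.4 and 90 children per arm. One daily t-test at 0.05 has 76% power. With complete data and within-child correlation r, the 7-day mean has variance (1 + 6r)/7 relative to one day, so the effective difference is 0.4 / √((1 + 6r)/7).

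| r | (1 + 6r)/7 | Effective d | Power |
|---|---|---|---|
| 0.3 | 0.400 | 0.632 | 99% |
| 0.5 | 0.571 | 0.529 | 94% |
| 0.6 | 0.657 | 0.493 | 91% |
| 0.8 | 0.829 | 0.439 | 83% |

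**The case against.** **A valid reading exists.** A t-test on each child's 7-day mean is sound, needs no mixed model and gives the 10 to 13% of Step 4. This stands as a possibility. The text does not state it, though, and the sentence before and section {20b} both work day by day.

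**The inputs are soft.** The correlations are assumed, some children may have about 5 days of data, and Guardian surveys describes a single caregiver pain observation where {20a} lists two ratings. With one caregiver rating the count is 2 × 7 = 14. This stands: 21 is a maximum, and the error rate must be given as a range.

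**The power contrast flatters the week-level test.** At d = 0.4 the chance that at least one of seven unadjusted days is significant is 97 to 99% (between-day correlation 0.6 to 0.4). At the implied d of about 0.52 a single day already has 93% power. This stands too. The gain from the model is one precise, interpretable estimate, not rescue of an underpowered plan.

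**Unadjusted supportive tests are common, and an analysis plan may say more.** True. The article states no rule for making claims from these p values. But it does name a method for these ratings and limits the better one by name, and Outcomes {12} calls the same ratings primary, which weakens the plea that they are only supportive.

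**A tempting stronger reading.** One might infer that all child-days are pooled in one t-test, which would treat a child's seven scores as independent. Nothing in the document suggests this. It acknowledges correlation among repeated measures, and its daily tests use one value per child.

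**Conclusion.** The point holds as a free or cheap improvement. For child worst pain and caregiver-observed pain, {20a} fixes a t-test without its unit or a multiplicity rule and leaves these repeated ratings out of a model already planned. On the per-day reading, the chance of at least one false p < 0.05 is roughly 27 to 55% under the assumed correlations, and lower with about 5 days, against about 10 to 13% for one week-level test per rating. At d = 0.4 and 90 per arm, week-level power is about 83 to 99% (r from 0.8 to 0.3), against 76% for a single day.

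A reader might infer that a spurious secondary finding is close to an even bet. The documents do not support that as a property of the plan: it needs the per-day reading, all 21 tests and only moderate correlation, and it disappears if each child's 7-day mean is tested. Nor is any daily test invalid in itself. The primary analysis is not affected by this point.

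**What to change.** In {20a}, Aim 1:

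- Fit the random-intercept model already planned for overall pain to each two-arm secondary pain rating: child worst pain, the caregiver ratings and time spent thinking about pain.
- Report one 7-day group difference with a 95% CI per rating. Show daily means descriptively, without p values.
- Either apply Holm across these contrasts or label them supportive. The model alone sets no multiplicity limit: four unadjusted contrasts would still give up to 1 − 0.95^4 = 18.5% if independent.
- Reconcile the secondary status of worst pain and the caregiver ratings in {20a} with Outcomes {12}, and give time spent thinking about pain a stated place.

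Anxiety should not simply be added to this list. It is scored before each dressing change, so the first home score precedes any home use of the headset.

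The cost is small: planned code is reused and no extra data or children are needed. What is lost is day-by-day p values for these ratings. Recruitment is expected to continue and no interim analysis is planned, so the change can be made before group results are seen.

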In the primary analysis, the mean child-reported VR engagement score in the VR-PAT group will be calculated along with a 95% confidence interval for each of the seven follow-up days. The intention-to-treat principle will again be used in the primary analysis by accounting for all subjects in the VR-PAT group in the calculation regardless of whether they actually use the VR device during dressing changes. Sensitivity analysis will also be conducted by imputing missing scores due to dropout and then recalculating the mean scores and their 95% confidence intervals. In the secondary analysis, the mean child-reported fun score and mean child-reported realism score will be calculated along with 95% confidence intervals for each of the 7 days. In addition, a linear mixed effect model with random intercept, dependent variable of child-reported VR engagement score, and independent variable of time will be fit to assess the trend of engagement score over the seven follow-up days. The coefficient of time will reveal the direction and magnitude of the trend. The same linear mixed effect models will be fit for child-reported fun scores and mean child-reported realism scores to assess their trends over time.

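### The exploratory group-by-time model and the secondary Aim 2 trend models have only a random intercept, so slope intervals are too narrow if children's slopes differ or daily scores are serially correlated

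*Protocol article*

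**What the plan says.** All of this is in the protocol article, Statistical methods {20a}.

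- **Aim 1, primary analysis.** Child-reported overall pain "will be compared between the VR-PAT and control groups during each of the first 7 days of follow-up" by two-sample t-test. No mixed model is involved.
- **Aim 1, overall difference.** For the average group difference over the week, "a linear mixed effect model with random intercept accounting for the correlation among repeated measures of pain scores will be fit".
- **Aim 1, trend.** As an exploratory step, to see whether the two arms follow different courses, "the same linear mixed effect model as above will be fit with the addition of interaction between the study group and time". The text then says: "The coefficient of the interaction term estimates the difference in the trend of pain scores over time".
- **Aim 2, primary analysis.** Mean engagement score with a 95% confidence interval on each of the seven days. No mixed model is involved.
- **Aim 2, secondary analysis.** "a linear mixed effect model with random intercept, dependent variable of child-reported VR engagement score, and independent variable of time will be fit", and "The same linear mixed effect models will be fit for child-reported fun scores and mean child-reported realism scores to assess their trends over time".

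No random slope, serial correlation, unstructured covariance or robust standard error is mentioned for any of these models.

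**The concern.** A random-intercept model lets children differ in their level of pain or engagement, but not in how fast it changes. It also makes day 1 as strongly correlated with day 7 as with day 2. Slopes are therefore judged almost entirely against day-to-day noise within a child, and most of the between-child variation in slope is left out of the standard error.

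Some slope variation is plausible in this population. The eligibility criteria admit children aged 6 to 17 with any pain score from 1 upward, from clinic, emergency department or inpatient unit. A child who starts at 1 has little room to fall, while a child who starts at 8 has a lot.

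At stake is the precision claimed for two secondary messages: whether VR changes the course of pain over the week, and whether engagement, fun and realism rise or fall with repeated use. With complete data the slope estimates stay unbiased. What can go wrong is the width of their intervals and the level of any test based on them.

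**Working it through.** **Inputs.** From the article: 7 daily surveys per child, random intercept only, 1:1 allocation, 89 children per group before dropout. The article gives no figure for the mixed models that could be reproduced; its sample size belongs to the daily t-test. It gives no numerical SD, no slope variation and no autocorrelation. Assumed here: residual SD s from 1.0 to 2.5 points, between-child slope SD τ from 0.1 to 0.4 points per day, complete data.

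**Formulas.** Centre the days at −3, …, 3, so the sum of squares is 9+4+1+0+1+4+9 = 28.

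- True variance of one child's fitted slope: τ² + s²/28.
- Variance used by the random-intercept model: the within-child mean square has expectation s² + 28τ²/6, and dividing by 28 gives s²/28 + τ²/6. Only a sixth of the slope variance is counted.
- R = (τ² + s²/28) / (s²/28 + τ²/6). The number of children cancels, so R is the same for a one-arm trend (Aim 2) and a difference between arms (Aim 1).
- Model SE / true SE = 1/√R. Rejection rate at nominal 5% = 2[1 − Φ(1.96/√R)].

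**Example, s = 1.5, τ = 0.3.** s²/28 = 0.0804. True variance = 0.0900 + 0.0804 = 0.1704. Model variance = 0.0804 + 0.0150 = 0.0954. R = 1.787, the SE ratio is 0.748, and the rejection rate is 14.3%.

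**Rejection rate (SE ratio) when the true trend, or difference in trend, is zero:**

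| Residual SD | τ = 0 | τ = 0.1 | τ = 0.2 | τ = 0.3 | τ = 0.4 |
|---|---|---|---|---|---|
| 1.0 | 5.0% (1.000) | 7.6% (0.904) | 14.3% (0.748) | 21.3% (0.635) | 26.9% (0.565) |
| 1.5 | 5.0% (1.000) | 6.2% (0.953) | 9.6% (0.850) | 14.3% (0.748) | 19.1% (0.667) |
| 2.0 | 5.0% (1.000) | 5.7% (0.972) | 7.6% (0.904) | 10.7% (0.823) | 14.3% (0.748) |
| 2.5 | 5.0% (1.000) | 5.4% (0.982) | 6.7% (0.935) | 8.7% (0.872) | 11.4% (0.808) |

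**Scale of τ.** Day 1 to day 7 is 6 steps, so τ = 0.1 to 0.4 means that individual change over the week has an SD of 0.6 to 2.4 points. As an illustration, a starting-pain SD of 2 (assumed) with a proportional fall of 50% to 100% gives τ = 2×0.5/6 to 2×1.0/6, about 0.17 to 0.33.

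**Serial correlation instead of differing slopes.** With parallel slopes but AR(1) residuals at correlation 0.2, 0.4, 0.6 or 0.8, the rejection rate is 8.9%, 14.0%, 19.8% or 25.7%.

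**Simulation check** (4,000 replicates, 89 per group). At τ = 0.3 the interaction test rejected in 15.2% and the one-arm trend test in 14.5%, against 14.3% from the formula at s = 1.5. The overall group coefficient stayed at 4.6% to 5.5% in every simulated scenario.

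**With a random slope.** In balanced data this is equivalent to a t-test on per-child slopes. At s = 1.5 the interaction test rejected in 5.1%, 5.0% and 5.0% at τ = 0, 0.3 and 0.5. This check of the remedy was run for differing slopes, not for serial correlation.

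**The case against.** The case for leaving the plan alone has several parts.

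- **The inflation is conditional.** This stands. With parallel slopes and independent residuals there is none, and with noisy daily scores and little slope variation it is under half a percentage point. A reader might infer that the models are bound to give false trend findings. The documents do not support that, because they contain no variance components.
- **The affected analyses have low standing.** This stands. The interaction is introduced as exploration, and both it and the Aim 2 time coefficient are described as estimating a trend, with no test level attached. A reader might infer that the Aim 2 answer on sustained engagement depends on the time coefficient. It does not: the Aim 2 primary analysis is the daily means with their intervals, and the trend model is a secondary addition.
- **The sentence that introduces the random intercept is about the overall difference.** This stands too. A reader might infer that the overall group coefficient is compromised, but with complete data it holds its level. The difficulty arises where the same structure is carried into the interaction and the Aim 2 trends.
- **Fading engagement is not shown.** Correct. Background and rationale {6a} reports steady enjoyment and rising realism and engagement in the pilot. Those are group-level statements, however, and leave open whether individual slopes differ.
- **An analysis plan that is not shown may settle the covariance.** This is fair for degrees of freedom and convergence rules. It does not remove the point, because the article itself names a random intercept for these models.

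**Conclusion.** The point holds in a limited form. The protocol article specifies a random intercept alone for the exploratory pain-by-time interaction and for the secondary engagement, fun and realism trends. If slopes differ between children, or neighbouring days are positively correlated beyond the intercept, the standard errors of those coefficients are too small. Over the assumed range of residual SD and slope SD, the intervals have about 57% to 98% of their proper width, and a nominal 5% test rejects in about 5% to 27% of null trials. The true position within that range cannot be read from the documents. The figures rest on 7 equally spaced days and complete data; dropout was not modelled.

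The trial's main conclusions are not in question: the daily t-tests, the Aim 2 daily means and the sample size do not use these models. The change is still worth making, because the trend results are likely to be reported with intervals and the correction costs very little.

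**What to change.** In the interaction model for pain and in the three Aim 2 trend models, replace the random intercept alone with one of the following, named in advance:

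- a random intercept and a random slope for day, allowed to correlate;
- an unstructured covariance over the 7 days (7×8/2 = 28 parameters), which also covers serial correlation; or
- the present model with cluster-robust standard errors by child, which also covers serial correlation.

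If the first or second does not converge, fall back to the random intercept with cluster-robust standard errors. The overall-difference model can stay as it is, though using the same structure throughout would be tidier.

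The cost is a line or two of wording, slightly wider intervals for the trends, and some risk of non-convergence, which the fallback covers. No new data or participants are needed. The Trial status section expects completion by April 30, 2027, so the change can be fixed before analysis.
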